#### Blinding

After giving this consideration, we think that is it not practically feasible to effectively blind the patient, therapist or researcher to the allocated treatment condition. Patients will be fully informed about the treatment options before providing informed consent. Researchers will have contact with the therapist about mental competency for informed consent, and hence will know whether the therapist is working on a ward or for an IHT-team. Information about whether the patient resides on the psychiatric ward or at home gives an indication of the allocated treatment. Therefore we have designed this RCT as an open label study.

### Interventions

#### Intensive home treatment

IHT is a treatment modality that addresses some of the imperfections of inpatient care by providing care in the patients’ home setting in the least restrictive environment; ‘normal’ life is disrupted as little as possible. In this way collaboration with and utilization of the patient’s social system can be maximised. During the first contact, patient, professionals and the most involved members of the patient’s social system discuss the problems or goals to be addressed during treatment. Collectively the priority of aims to achieve will be determined. In addition, the ways in which to achieve the aims, who takes responsibility for which part of the treatment plan and with whom the progress will be evaluated after 3 and 6 weeks is collectively decided. IHT professionals have the capacity to visit the patient at home, up to three times per day. The patient (and his/her relatives) can reach the IHT professionals 14 h per day, seven days a week (from 8.30 AM till 10:00 PM), while PES can be reached outside these hours if necessary. The IHT team starts as soon as possible after treatment allocation and remains involved until the crisis is resolved, for an average duration of 6 weeks. After IHT, the patient is referred to appropriate follow-up treatment if necessary.

The IHT team is a multidisciplinary team consisting of a psychiatrist, a psychiatry resident, a psychologist and (social) psychiatric nurses. All members of the team received additional education in family and relational treatment. Professionals of the IHT can provide:Assessment: psychiatric diagnostic, risk taxationPsycho-education to the patient and his relativesSupport in structuring patient’s daily life, and in solving social and financial problemsSupportive and cognitive behavioural interventionsPharmacotherapySupport and empowerment to patient’s informal care system so they will be able to sustain careSupport a more gradual transition between in-patient care and low intensity out-patient care if the patient is admitted to a psychiatric wardReferral, if necessary, to specific treatment settings

#### Care as usual

Standard crisis care often includes admission or low intensity (i.e. less than 3 times a week) outpatient treatment. If admitted, the patient’s environment is generally highly structured at the outset (a closed ward, for example), and becomes less structured as the patient’s condition improves (open ward). This may be followed by day treatment and follow-up treatment in an outpatient department [30, 31]. Patients in the CAU condition typically receive a combination of inpatient (first phase) and low-intensity outpatient (second phase) treatment. The length of the different phases depends mostly of the severity of the symptoms, presence of danger, social factors like housing and availability of support by family and friends. Professionals at a psychiatric ward are psychiatrists, medical doctors, psychologists, nurses and other mental health professionals. No treatments are withheld from patients in CAU except IHT.

The contents of treatment can be similar as provided by the IHT professionals but in a different setting. Benefits for the patient of being admitted can be:The feeling of being in a safe environment because professionals are nearNot being dependent on help from family or friendsBeing liberated from role obligations present in the home setting

### Measurements

Measurements will be conducted at the start of the treatment (T0) and at 6, 26 and 52 weeks follow-up (T1, T2, T3; see Table 1). All self-report questionnaires, potential effect moderators and demographic variables will be collected using several assessment methods. Once written informed consent has been provided, the research team will conduct the data collection of the participating patient through structured interviews and by collecting specific data from the EHR system in both mental health care organisations. The data collection of the relative and professional involved in the treatment will be conducted using a web-based platform. From the pilot experience it is known that the baseline interview will take about two hours and that the follow-up interviews take about one and a half hour to complete. To compensate patients for their time and efforts, patients receive a remuneration of €10 for the completed baseline questionnaire. For the follow-up questionnaire the patient will receive a remuneration of €15 (6 weeks), €20 (26 weeks) and €25 (12 months).

**Table 1 Tab1:** Measurement instruments

					Timetable (weeks)			
Categories	Subcategories	Instruments	About	By	Base-line	6	26	52
Demographics	Diversity of questions	–	Pat & Re	All	x			
Safety	Harm, violence, and suicide	SDAS (short)	Pat	Prof.	x	x		
Psychiatric symptoms	Diagnostic Classification	DSM-IV-TR /V	Pat	Prof.	x			
	Psychosocial functioning	HoNOS	Pat	Prof.	x	x		
	Symptoms	BSI (short)	Pat	Res	x	x		x
	Symptoms	BPRS	Pat	Res	x	x	x	x
Treatment satisfaction	Patients’ satisfaction	ZUF-8	Pat	Res		x		x
	Patients’ treatment satisfaction	TPQ	Pat	Res		x		
	Relatives’ satisfaction	CIS	Re	Re		x		x
	Professionals’ satisfaction	Self-developed	[name].		x		
Social support & Network extent	Patients’ perspective	Personal recovery	Pat	Res	x	x	x	x
	Relatives’ perspective	BES	Re	Re	x	x		x
Self-efficacy		MHCS	Pat	Res	x	x	x	x
Quality of life		EQ-5D-5L	Pat	Res	x	x	x	x
		SF-12	Pat	Res	x		x	x
		MANSA	Pat	Res	x			x
Substance use	Alcohol	AUDIT	Pat	Res	x		x	x
	substance abuse	MATE-I	Pat	Res	x		x	x
Cost-effectiveness	direct medical contacts	TiC-P	Pat	Res	x		x	x
	Delivered informal care and support by relative	iVICQ (short)	Re	Re	x	x		x
	Absenteeism from work	PRODISQ (short)	Pat	Res.	x		x	x
Supplementary	Symptoms	S&P	Pat	Prof.	x			

Pat = participant/patient; Re = relative; Prof. = professional; Res = researcher; Self = self report; Int = Interview

AUDIT = Alcohol Use Disorder Identification Test (AUDIT); BES = Betrokkenen Evaluatie Schaal [Stakeholders Evaluation Scale]; BPRS = Brief Psychiatric Rating Scale; BSI = Brief Symptom Inventory; CIS = Contact, Information and Support; CSQ = Client Satisfaction Questionnaire; DSM = Diagnostic and Statistical Manual of Mental Disease; EQ-5D-5L = European Quality of Life, 5 Dimensional, 5 level; HoNOS = Health of the Nation Outcome Scale; iVICQ = iMTA Valuation of Informal Care Questionnaire; MANSA = Manchester Short Assessment of Quality of Live; MATE = Measurements in the Addictions for Triage and Evaluation; MHCS = Mental Health Confidence Scale; PRODISQ = Productivity and Disease Questionnaire; SDAS = Social Dysfunction and Aggression Scale; SF-12 = Short Form health survey; S&P = Staging and Profiling; TPQ = Treatment Perception Questionnaire; TiC-P = Trimbos Institute and Institute of Medical Technology Questionnaire for Costs Associated with psychiatric Illness; ZUF-8 = Zufriedenheit-8 (Satisfaction scale)

The informatics team in both mental health care organisations will assist in data collection from the EHR system. The research team provides a list of participants’ surnames, date of birth, a unique project number for each participant and a standardised schedule of the information required for each participant. The required data will be specified with the time period for which data is needed. By providing the data only by research number data risks from transferring identifiable patient data will be minimized.

### Demographic variables

At baseline, participants complete questions concerning basic demographic details; those questions include age, gender, country of origin, parents or relative’s country of origin, domestic situation, education level, occupational status and income. Drug history will be requested from the pharmacy (with participant’s consent), while the use of mental health care in the year before allocation to this study will be collected from the EHR system. The use of other health care will be collected from the CBS data (with participant’s consent) and the TiC-P instrument.

### Primary outcome measure

The number of hospitalisation days in the 52 weeks after randomisation is the primary outcome measure. This includes the duration of the initial admission at baseline, and any subsequent psychiatric admission during the 12 months follow-up period of the study. Data will be collected from the EHR system of both mental health care organisations.

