### Study procedure

#### Recruitment

Arkin and GGZ inGeest are the two largest mental health care organisations in Amsterdam, the Netherlands and provide in- and outpatient psychiatric care in Amsterdam for children and adults of all ages. The Psychiatric Emergency Service Amsterdam (PES) is a cooperation between these two organisations. Referrers to PES include general practitioners, other mental health professionals and the police. A professional of PES performs psychiatric assessments, prepares a treatment plan with the patient in cooperation with his family and other professionals, and provides care as described in the treatment plan. PES is available 24 h a day, 7 days a week. The IHT teams are part of PES.

In this study, participants are recruited via IHT teams and the in-patient facilities of Arkin and GGZ inGeest between 8.30 AM and 10.00 PM. During the night, between 10:00 PM and 8:30 AM, PES Amsterdam is functioning as a gatekeeper for Arkin and GGZ inGeest. During night hours patients assessed by this service will receive CAU, i.e. voluntary or involuntary psychiatric admission or community-based care, with support from PES if necessary. The next day, these patients will be screened to check if they meet the in/exclusion criteria for this study. If participants have been admitted to a psychiatric ward during the weekend, they will be screened for study participation the next working day.

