All patients who meet the inclusion criteria, none of the exclusion criteria, and who are mentally competent to give an informed consent will be approached by the research team and receive information about the study. The patient and his relatives will receive an information folder describing the CAU and IHT interventions and study procedures. An appointment will be made to inform the patient about treatment allocation, answer any questions the patient may have regarding the study and to collect the written informed consent if possible. Consent will be sought regarding (1) the treatment condition they are allocated to, (2) the baseline and follow-up measurements, (3) to inform their relatives, (4) informing their general practitioners, other mental health professionals, (5) informing and asking their pharmacist about drug use, (6) to request and use their data from Statistics Netherlands (Centraal Bureau voor de Statistiek (CBS)). A patient can also participate in this study by giving informed consent to using existing data sources such as their Electronic Health Record (EHR) and CBS data only – EHR data is sufficient to test our primary hypothesis (number of hospitalisation days).

If the patient hesitates about providing informed consent, (s)he will have 5 more days to decide to participate. Only after providing written informed consent, baseline measurements are administrated. If a patient decides not to provide informed consent, (s)he is not included in the study (and can receive any treatment deemed necessary).

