#### Cost-effectiveness calculations

The economic evaluation will be conducted as a cost-utility analysis using quality adjusted life years (EQ-5D/QALYs) as a generic measure of health gains. We will use the EQ-5D tariffs from both the UK [60] and the Netherlands [61]. Health utilities based on the SF-12 will be calculated using the Brazier’s algorithm [62]. The primary endpoint will be 12 months post allocation for the cost-utility analysis. The cost-utility analysis will be conducted and reported in agreement with the Consolidated Health Economic Evaluation Reporting Standards (CHEERS). The trial’s follow-up measurements do not exceed the time horizon of one year and therefore neither costs nor effects will be discounted. Sensitivity analyses will be directed at uncertainty in the main cost drivers. We will consider five types of costs: (1) the costs of offering the intervention, (2) costs stemming from health care uptake (e.g. hospitalisation) including the costs of medication, (3) patients’ out-of- pocket costs, (4) costs stemming from productivity losses due to absenteeism and reduced efficiency while at work (if the patient holds a job) and 5) costs of informal care network. We will perform the cost-utility analysis from at least two perspectives: (1) Societal perspective, (2) healthcare provider perspective. Volumes of direct medical contacts will be collected using the TIC-P and PRODISQ-short version, using the EHR of the participating institutions, and using external data sources such as from CBS if possible. These different but overlapping sources will be used in order to assess the reliability of the data sources. Delivered informal care and support by relatives will be measured using the iVICQ-short version. Unit costs for delivered care will be obtained from most recent costing manuals for the societal perspective, and unit costs for the healthcare provider perspective will be obtained from the Dutch Health Care Authority (NZa) averaged costs. Data presented will include incremental cost-effectiveness ratio’s (incl. Gains in QALY), and cost effectiveness acceptability curves. Uncertainty around the reported parameters will be assessed using non-parametric bootstrapping.

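### The primary outcome covers any psychiatric admission in the year, but its only named source is the records of two organisations, and no check on days elsewhere is tied to the primary result.

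*Protocol article*

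**What the plan says.** The Primary outcome measure section of the protocol article states: "The number of hospitalisation days in the 52 weeks after randomisation is the primary outcome measure". It includes the initial admission and "any subsequent psychiatric admission during the 12 months follow-up period of the study", with no limit to particular facilities. The same section then fixes the source: "Data will be collected from the EHR system of both mental health care organisations". The Consent and mental competence section allows participation on existing data alone, on the ground that "EHR data is sufficient to test our primary hypothesis (number of hospitalisation days".

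Under Recruitment, Arkin and GGZ inGeest "are the two largest mental health care organisations in Amsterdam". The inclusion criteria require residence in the area at entry. The article gives no rule for patients who move or are admitted elsewhere.

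Two further sources are collected. Under Demographic variables, "The use of other health care will be collected from the CBS data", with consent, and from the TiC-P. Under Cost-effectiveness calculations, "Volumes of direct medical contacts will be collected using the TIC-P and PRODISQ-short version", together with the EHR and, if possible, external sources such as CBS. That section plans to compare these overlapping sources for reliability. Neither CBS nor TiC-P is linked to the primary outcome. The Statistical analysis section plans an over-dispersed Poisson mixed model for the primary outcome and multiple imputation for missing data.

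**The concern.** The definition is wider than the source. Calling two organisations the largest implies that others exist, and residence is fixed only at entry. A count built from a record search adds nothing for an admission that the records do not hold. The result for that patient is a low or zero count that looks complete. The sample size section expects little missing data because the outcome comes from the EHR, and the only loss it names is active withdrawal of up to 5%. A patient who moves away or is admitted elsewhere has not withdrawn, so nothing in the plan would mark that follow-up as incomplete.

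This is the sole primary outcome, and the trial hypothesis is a 33% reduction in it. If the two arms differ in the proportion of days captured, the estimated ratio is biased, and the plan has no step that would reveal it. The economic evaluation could also reach a different view of inpatient use from the primary analysis of the same trial.

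**Working it through.** **Definition against source.** The definition has no facility limit. The source is the EHR of two organisations. The other sources (CBS and TiC-P) are assigned to other health care use and to costs. The reliability comparison sits under the cost-effectiveness calculations only. No text closes the gap for the primary outcome.

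**The plan's own figure.** Inputs from Sample size calculation: 40 days (SD 40) for IHT, 60 days (SD 55) for CAU, two-sided alpha 0.05, power 0.80, 2:1 allocation, 5% withdrawal and 5% added for cross-over.
- Common SD = sqrt((40² + 55²)/2) = 48.09, so d = 20/48.09 = 0.416.
- A two-sample t calculation at 2:1 gives 206.1 patients in total.
- Inflation: 206.1/0.95 × 1.05 = 227.8; 206.1/0.95² = 228.4; 206.1/0.90 = 229.0.

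The stated 230 (153 + 77) is reproduced closely. This point does not affect it.

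**Effect of missed days.** The share of days elsewhere is not given, so the shares below are assumptions. Let f1 and f0 be the shares missed in IHT and CAU.
- Observed means: 40(1 − f1) and 60(1 − f0).
- Observed ratio: 40(1 − f1) / [60(1 − f0)]. If f1 = f0, the shares cancel and the ratio stays 0.667.
- Power, on the difference in means used for the sample size, by normal approximation: 153 × 0.95 ≈ 145 and 77 × 0.95 ≈ 73 patients. SE = sqrt(1600/145 + 3025/73) = 7.24 days, so power with no loss = Φ(20/7.24 − 1.96) = 0.79.

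Power is shown twice: with the SDs kept at 40 and 55, and with each SD reduced in proportion to its mean.

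| Assumed share missed, IHT / CAU | Observed means | Difference (days) | Ratio | Apparent reduction | Power, SDs fixed | Power, SDs scaled |
|---|---|---|---|---|---|---|
| 0 / 0 | 40 / 60 | 20 | 0.667 | 33.3% | 0.79 | 0.79 |
| 5% / 5% | 38 / 57 | 19 | 0.667 | 33.3% | 0.75 | 0.79 |
| 10% / 10% | 36 / 54 | 18 | 0.667 | 33.3% | 0.70 | 0.79 |
| 20% / 20% | 32 / 48 | 16 | 0.667 | 33.3% | 0.60 | 0.79 |
| 0 / 5% | 40 / 57 | 17 | 0.702 | 29.8% | 0.65 | 0.69 |
| 0 / 10% | 40 / 54 | 14 | 0.741 | 25.9% | 0.49 | 0.55 |
| 5% / 0 | 38 / 60 | 22 | 0.633 | 36.7% | 0.86 | 0.87 |
| 10% / 0 | 36 / 60 | 24 | 0.600 | 40.0% | 0.91 | 0.92 |

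Bias in the ratio needs unequal proportions missed. The one-arm rows are deliberate extremes, and they point in opposite directions.

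**The case against.** A single objective source applied in the same way to both arms is a defensible choice in an open-label trial. Recruitment runs through the IHT teams and inpatient facilities of the same two organisations, so the initial admission probably falls mostly within their records, and any loss would fall mainly on later admissions. The phrase about the two largest organisations does not show that others run acute beds used by these patients. Interviews at 6, 26 and 52 weeks could bring a move to light for those interviewed. The reliability comparison in the economic evaluation includes the EHR and is a partial safeguard. All of this stands. It limits the likely size of the problem but does not connect any check to the primary result.

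Four stronger readings are tempting, and the documents do not support them.
- A reader might infer a rule that days elsewhere count as zero. The article states no such rule. It is an inference, though a sound one, about what a record search returns.
- A reader might infer that data already collected would reveal these days. They could, but not for everyone. CBS data need consent and are used if possible, patients consenting to existing data only have no TiC-P, and neither source is said to yield dated psychiatric inpatient days.
- A reader might infer that CAU loses more because its patients have more admissions. More admissions mean more missed days, not a higher proportion missed, and only the proportion biases the ratio.
- A reader might infer a definite loss of power. The low values in the table assume loss in CAU only. With equal loss and SDs that shrink in proportion, power stays at 0.79.

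**Conclusion.** The mismatch between definition and source is plain on the text. Followed as written, the plan would omit days spent elsewhere without marking them as missing. How much this matters cannot be derived from the documents, and neither can the direction. With equal proportional loss the rate ratio, which is the natural contrast for the planned Poisson model if the usual log link is used, does not change. An assumed 10% loss in one arm only moves the apparent reduction from 33% to 26% (CAU only) or 40% (IHT only). These figures rest on the protocol's planning means and on assumed shares. The point is worth acting on because it concerns the only primary outcome and the repair is cheap, not because a large bias has been shown.

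**What to change.** Three changes.
1. Keep the EHR count at the two organisations as the primary source, and state that the primary outcome measures psychiatric inpatient days in those organisations.
2. Pre-specify a sensitivity analysis of the primary result that adds psychiatric inpatient days elsewhere, from CBS data where consented and from the week 26 and 52 TiC-P where interviewed. Report the added days and the coverage of each source by arm.
3. Treat patients known to have moved out of the area as incompletely observed from that date, through an exposure offset or imputation, not as having zero days afterwards.

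The cost is further analysis of data whose collection is already planned, plus recording known move dates. The added data bring recall error in an open-label trial, and coverage is incomplete because of CBS consent and missing interviews. For that reason they belong in a sensitivity analysis and should not replace the uniform primary count. Whether CBS and TiC-P can supply psychiatric inpatient days in usable form should be confirmed before the analysis is fixed.

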### Secondary outcome measures

Safety:

Social Dysfunction & Aggression Scale (SDAS); this 4-item questionnaire assesses harm, including self-inflicted, violence, and suicide attempts [32].2)Psychiatric symptoms:DSM-IV or V classification [33, 34].Health of the National Outcomes Scales (HoNOS); 15-item scale measure of the health and social functioning of people with severe mental illness [35–37].Brief Symptom Inventory (BSI) ; 53-item self-reported 5 point (0–5) Likert-type scale measuring the extent to which individuals have been disturbed by certain mental health symptoms [38].Brief Psychiatric Rating Scale (BPRS); 24-item interview based scale to measure psychiatric symptoms [39, 40].3)Treatment satisfaction:The Client Satisfaction Questionnaire (CSQ): Zufriedenheit 8 items (ZUF-8) [41, 42], an open access variant of the CSQ-8 [43]) and the Treatment Perceptions Questionnaire (TPQ) [42, 44, 45].Family Contact, Information and Support (C.I.S.) Questionnaire. Relatives’ satisfaction about patients’ treatment and the contact with the professionals is assessed using the questionnaire [46].The professional will be asked to give on a 10-point scale an appreciation of the treatment. This self-developed questionnaire assesses overall treatment satisfaction, treatment compliance and treatment plan and healthcare process.

